### Randomization and blinding

#### Randomization

Randomization will occur during or immediately after the baseline visit. An independent statistician from a third-party statistical agency will use SAS statistical software (SAS Institute, Inc.; Cary, NC, USA) to generate random sequences, perform random grouping, and code drugs; patients will be randomly categorized into two groups in a 1:1 ratio per the randomized sequence table. The participants who received placebo will be considered as controls. The distribution scheme of hiding and implementing known as the opaque envelope method will be used to hide random sequences. The random code of the drug will be the unique identification code of the participants. The letter will be collected together with the case report form (CRF) after the end of the trial.

#### Blinding

Blindness will be ensured between the investigators (doctors) of the study and subjects (patients). In the drug preparation stage, the placebo is specially made by the probiotic manufacturer. Except that it does not contain probiotics, other excipients are the same, and the appearance and packaging of the drugs will be consistent. For blinding purposes, participants of the two groups will receive the same number of capsules daily and will be unaware of their own and others’ grouping before, during, and after the orthopedic surgery. As the medication will be encapsulated and provided by an independent nurse per the random codes, the investigator, intraoperative attending anesthesiologist, evaluator, and data analyst will be unaware of the allocation until the study is completed or a patient is intentionally unblinded. The aforementioned independent statistician will not be involved in the study process and statistical analysis of the test results.

An unblinding (emergency) envelope contains the information of the drugs to be taken by the subjects with their corresponding numbers. This will be sent to the researchers together with the study drug for use in case of emergency. It is forbidden for clinical efficacy evaluators to ask drug managers and subjects for product information to avoid influencing the efficacy evaluation due to subjective factors. In case of a medical emergency, which requires the identification of an individual patient’s treatment, the investigators will be permitted to open the respective emergency envelope. A justification must be documented in the patient’s medical record and CRF. Serious adverse events will recorded for further analysis at the end of the trial, and investigators will explore the correlation between these events and patients’ healthcare records.

### Interventions

Figure 1 shows the schedule of major study events for each visit. Elderly patients planning to undergo orthopedic surgery will be included in this study. The surgery will be performed within 2 days after screening. The drug will be used a day before operation until 6 days postoperatively. The probiotic group will be treated with Peifeikang (Bifidobacterium triple viable powder, 210 mg per capsule), while the control group will be treated with placebo in the same package. The drug will be taken orally, four capsules at a time, twice a day, and the postoperative cognitive function will be evaluated using a neuropsychological test. If participants request to withdraw from the trial, we will discontinue the allocated intervention for the given trial participants. Adherence to interventions primarily refers to patient self-management adherence. No concomitant care or interventions will be permitted during this trial.

### Participant timeline

Figure 1 presents the schedule for enrollment, interventions, assessments, and visits of participants.

Cognitive function assessment: 1 day before operation: Mini-Mental State Examination (MMSE) screening, digit span test, digit symbol test, Wechsler Memory Scale (WMS), visual regeneration, and digital connection test will be performed. 7 days after operation or before discharge: digit span test, digit symbol test, WMS, visual regeneration, and digital connection tests will be performed again. 7 days after operation: POD will be assessed using the CAM, which includes acute onset, inattention, disorganized thinking, and abnormal consciousness. The diagnosis of delirium by CAM requires the presence of features 1 and 2 and either 3 or 4. Table 2 presents the specific content.

**Table 2 Tab2:** Specific content of the Confusion Assessment Method

The Confusion Assessment Method (CAM)	
Feature 1	Acute change in mental status with a fluctuating course Is there evidence of an acute change in mental status from the patient’s baseline? Did this behavior fluctuate during the past day, that is, tend to come and go or increase and decrease in severity? This feature is usually obtained from a family member or nurse and is shown by positive responses
Feature 2	Inattention Do the patients have difficulty focusing attention, for example, being easily distractible, or having difficulty keeping track of what was being said?
Feature 3	Disorganized thinking This feature is shown by a positive response to the following question: Was the patient’s thinking disorganized or incoherent, such as rambling or irrelevant conversation, unclear or illogical flow of ideas, or unpredictable switching from subject to subject?
Feature 4	Altered level of consciousness Overall, how would you rate this patient’s level of consciousness? (alert [normal], vigilant [hyperalert], lethargic [drowsy, easily aroused], stupor [difficult to arouse], or coma [unarousable])

The diagnosis of delirium by CAM requires the presence of features 1 and 2 and either 3 or 4

We will also assess the long-term cognitive status using a modified cognitive state telephone interview (TICS-m) 1 month after surgery. TICS-m has been used to screen for dementia and mild cognitive impairment. The TICS-m score ranges from 0 to 48. The higher the score, the better the function. An evaluator will comprehensively evaluate the patient’s condition according to the patient’s medical history, clinical observation, current scale evaluation, and information provided by family members or nursing staff.

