Before surgery, the doctor will conduct medical visits for up to 40 min and complete the scale for each patient; furthermore, they will inform the patients that they will be followed up and observed for several consecutive days after surgery. If necessary, the doctor will communicate with the patient through WeChat to understand their latest situation in addition to communicating through phone calls. One day before surgery, the anesthesiologist will record each patient’s general information, including sex, years of education, BMI, dietary habits, history of disease, medication, and surgery. During surgery, blood pressure fluctuations are maintained within 20% of the baseline blood pressure level. Anesthesiologists will record the volume of infusion, estimated blood loss, and urine output and assess the need for a blood transfusion. Similarly, the duration of surgery, anesthesia, and hospital stay after surgery are recorded. After surgery, an analgesia pump will be used for intravenous self-analgesia (uniformly prepared by the pharmacy). Patient-controlled analgesia and or nerve block would be used for postoperative analgesia in all patients to maintain a VAS score of less than 3. The PCIA pump includes the following analgesics: sufentanil citrate 100 μg and flurbiprofen axetil 100 mg which are prepared into 0.9% sodium chloride, in a total volume of 100 ml. All patients receive a 1.5 ml on-demand bolus with a lockout interval of 15 min. The infusion was started immediately after suturing the skin incision and lasted 48 h. We use morphine as rescue drug, which is given according to the patient’s pain situation. At the same time, the drug dosage of the patient’s analgesia pump used and morphine dosage are recorded. Three months after operation, the same doctor will call the patient again for follow-up. All data collected during this clinical study will be entered and/or filed in the patients’ CRFs. The patients’ study participation must be documented appropriately in the CRF with their study number, subject number, date of subject information, informed consent, and date of each visit. Source data will be filed according to the GCP guidelines. The data manager will be responsible for data processing, following the sponsor’s standard operating procedures.

Regular monitoring will be conducted to ensure that the data are adequate, accurate, and complete. The database will be locked only after the completion of quality assurance procedures.

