### Statistical analysis

All statistical tests are conducted by two-sided test, and the difference tested will be considered to be statistically significant if *P* ≤ 0.05(unless otherwise specified). The primary outcome measure will be statistically analyzed by chi-square or Fisher exact probability. Secondary outcome measures will be tested by group t-test. The description of quantitative indicators will calculate the mean, standard deviation, median, minimum, and maximum. The number and percentage of patients are used to statistically describe the demographic information, medical history, combined diseases and symptoms, physical examination, operation time, etc. According to the numerical characteristics of variables, *t*-test/Wilcoxon rank sum test is used to compare the quantitative data of age, height, and weight between the two groups; chi-square test/exact probability method is used to compare the categorical variables such as gender, medical history, combined diseases and symptoms, physical examination and so on.

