### Secondary outcome measures

Secondary outcomes comprise the following:Incidence of POD

Postoperative delirium will be assessed 7 days after surgery using the Confusion Assessment Method (CAM), which includes acute onset, inattention, disorganized thinking, and abnormal consciousness. The diagnosis of delirium by CAM requires the presence of features 1 and 2 and either 3 or 4 (Table 2).2)Cognitive status 1 month after surgery

The cognitive status will be determined based on a telephone interview and will be evaluated via TICS-m in 1 month after surgery.

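### The 1-month TICS-m score is assigned an unadjusted t-test although day -1 cognitive scores and years of education are collected: a valid analysis that gives up precision on a secondary outcome

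*Protocol article*

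**What the plan says.** Participant timeline introduces the 1-month assessment: "We will also assess the long-term cognitive status using a modified cognitive state telephone interview (TICS-m) 1 month after surgery". The outcome appears again under Secondary outcome measures: "The cognitive status will be determined based on a telephone interview and will be evaluated via TICS-m in 1 month after surgery". Participant timeline describes the instrument: "The TICS-m score ranges from 0 to 48", with higher scores meaning better function and no cut-off given. That section schedules TICS-m at 1 month only.

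The test is fixed under Statistical analysis: "Secondary outcome measures will be tested by group t-test". No covariate is named there. Additional analyses says that further analyses will use the same methods, so no adjusted model appears in the article.

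Two kinds of relevant baseline information are collected. Participant timeline schedules, for the day before operation, "Mini-Mental State Examination (MMSE) screening, digit span test, digit symbol test, Wechsler Memory Scale (WMS), visual regeneration, and digital connection test". Data collection and management says that "the anesthesiologist will record each patient’s general information, including sex, years of education, BMI" and other items on the same day. The Consent section states that baseline data are obtained before randomisation. The primary outcome already uses each patient's preoperative scores through the Z-score definition of POCD.

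**The concern.** Two secondary outcomes are listed. Delirium by CAM is a yes/no outcome, so TICS-m is the only one of the two that a t-test fits. A single 1-month score in patients aged 65 or over can be expected to reflect how well each patient performed before surgery, and how much schooling they had, as well as anything that surgery or treatment did. An unadjusted comparison leaves that variation in the error term even though measurements that could remove part of it are already in the case report form.

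At stake is the width of the confidence interval for the 1-month difference. The sample size was set for POCD at day 7 and nothing was sized for TICS-m. With the patient numbers fixed, precision on this outcome can come only from the analysis.

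**Working it through.** **1. The plan's own sample size.** Inputs from the Sample size section: 25% against 10%, alpha 0.05, power 0.80, and from Statistical analysis, two-sided tests. With the pooled chi-square formula and a mean rate of 0.175:

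n = [1.960 × √(2 × 0.175 × 0.825) + 0.842 × √(0.25 × 0.75 + 0.10 × 0.90)]² / 0.15² = (1.053 + 0.443)² / 0.0225, which rounds up to 100 per arm.

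This reproduces the stated 100. The stated 110 per arm is 100 × 1.10. No SD, effect size or power is given for TICS-m.

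**2. Evaluable patients at 1 month.** Applying the stated 10% loss to 110 gives 110 × 0.90 = 99 per arm.

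**3. The stated analysis.** For a two-sample t-test with 99 per arm, two-sided 5% and 80% power, the normal approximation gives (1.960 + 0.842) × √(2/99) = 0.398 SD. The exact t calculation gives 0.400 SD. With 100 per arm the normal approximation gives 0.396 SD, so the choice between 99 and 100 does not matter.

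**4. The adjusted analysis.** If the baseline covariates explain a share R² of the variance of TICS-m, the residual variance is (1 − R²) × SD². Then:

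- detectable difference = 0.400 × √(1 − R²)
- reduction in confidence interval width = 1 − √(1 − R²)
- equivalent sample size multiplier = 1 / (1 − R²)

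The documents give no R², so it is **assumed** over a range that includes low values. The power column uses a true difference of 0.30 SD, also an assumption, for illustration.

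| Assumed R² | Detectable difference (SD) | CI narrower by | Equivalent n multiplier | Power at 0.30 SD |
|---|---|---|---|---|
| 0 (t-test) | 0.400 | – | 1.00 | 56% |
| 0.09 | 0.382 | 5% | 1.10 | 60% |
| 0.16 | 0.367 | 8% | 1.19 | 63% |
| 0.25 | 0.347 | 13% | 1.33 | 68% |
| 0.36 | 0.320 | 20% | 1.56 | 75% |
| 0.49 | 0.286 | 29% | 1.96 | 84% |

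**5. Cost if the covariates predict nothing.** Two covariates use two of 2 × 99 − 2 = 196 degrees of freedom, which is negligible.

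**6. Which cognitive covariate.** Table 1 excludes patients with MMSE below 24, so MMSE enters with a truncated range and may predict less than the battery. The primary outcome definition counts high values on the connection (number lines) test as worse and low values on the other four as worse. That test must therefore change sign before the five scores are averaged.

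**The case against.** The strongest reply is that nothing is stated wrongly. Under randomisation the unadjusted t-test is unbiased and keeps its type I error, and adjustment is a choice about efficiency. That stands, and it limits the point to precision. It does not remove the point, because the article names the test rather than leaving it to an analysis plan, and a better use of data already collected is available.

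The gain may also be small. The battery is a different instrument from TICS-m, and the entry criteria exclude low MMSE and neurological disease, which may weaken the correlation. At R² = 0.09 the interval narrows by only 5%. That stands too.

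A reader might infer more than the documents support:

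- **That most of the spread in TICS-m is prior cognition and schooling.** The documents give neither an SD nor a correlation, and none of the R² values assumed here reaches one half.
- **That chance imbalance at baseline is a second, separate harm.** The standard error of the t-test already allows for such imbalance. This is the precision point again.
- **That TICS-m is the only cognitive comparison after day 7.** The Abstract mentions neuropsychological tests at 1 month, and both the Abstract and Objectives name the incidence of POCD at 1 month as a secondary objective. Participant timeline and Secondary outcome measures give only TICS-m at that time.

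The last item also shows that reading the outcome as a numeric score is an inference. It rests on the 0 to 48 scale, the absence of a cut-off and the choice of a t-test. If an incidence is meant at 1 month, neither the t-test nor an ANCOVA fits it.

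**Conclusion.** The point holds as a missed, nearly free gain in precision on one secondary outcome. It is not an error of validity, and the primary conclusion on POCD at day 7 is unaffected. With 99 evaluable per arm, the detectable difference would fall from 0.40 SD to somewhere between 0.38 and 0.29 SD for an assumed R² of 0.09 to 0.49. The true position in that range is unknown from the documents. The conclusion assumes that TICS-m is analysed as a total score and that the day -1 data are taken before randomisation, as the Consent section states.

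**What to change.** In Statistical analysis, replace the group t-test for TICS-m with this: the main analysis of the 1-month TICS-m total score is an ANCOVA on treatment arm, with the day -1 mean standardised battery score (connection test sign-reversed) and years of education as covariates. Report the adjusted mean difference with its 95% CI, and keep the unadjusted t-test as a supportive analysis. Name the single battery score and not a choice between it and MMSE, so that the covariate cannot be picked after the results are seen. Settle the wording before unblinding.

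Reconcile the 1-month POCD incidence wording in the Abstract and Objectives with the TICS-m outcome in Participant timeline and Secondary outcome measures. If an incidence is intended at 1 month, it needs its own definition and a test suited to a binary outcome.

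The cost is a few sentences of text. The covariates are already collected, and no extra visits, staff or patients are needed.

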### Sample size

According to previous studies, the incidence rate of POCD after a major surgery was 25% [12], and the estimated application of probiotics could reduce it to 10%. According to alpha = 0.05, Power = 0.80, PASS 11 will be applied. The calculated sample size is *n* = 100 cases, with a shedding rate of 10%. The sample size of each group is *n* = 110 cases.

### Data collection and management

This study is a multicenter clinical trial. All data collection physicians will be specially trained by assessors. We will conduct online meetings regularly to share the progress of the trial and discuss the problems that we encounter during the project. Moreover, we will conduct field visits to subcenters for quality control. We shall also organize the trial data regularly to check for any missing data. Furthermore, to promote data quality, we intend to apply other methods and call the participants for follow-up.

Before surgery, the doctor will conduct medical visits for up to 40 min and complete the scale for each patient; furthermore, they will inform the patients that they will be followed up and observed for several consecutive days after surgery. If necessary, the doctor will communicate with the patient through WeChat to understand their latest situation in addition to communicating through phone calls. One day before surgery, the anesthesiologist will record each patient’s general information, including sex, years of education, BMI, dietary habits, history of disease, medication, and surgery. During surgery, blood pressure fluctuations are maintained within 20% of the baseline blood pressure level. Anesthesiologists will record the volume of infusion, estimated blood loss, and urine output and assess the need for a blood transfusion. Similarly, the duration of surgery, anesthesia, and hospital stay after surgery are recorded. After surgery, an analgesia pump will be used for intravenous self-analgesia (uniformly prepared by the pharmacy). Patient-controlled analgesia and or nerve block would be used for postoperative analgesia in all patients to maintain a VAS score of less than 3. The PCIA pump includes the following analgesics: sufentanil citrate 100 μg and flurbiprofen axetil 100 mg which are prepared into 0.9% sodium chloride, in a total volume of 100 ml. All patients receive a 1.5 ml on-demand bolus with a lockout interval of 15 min. The infusion was started immediately after suturing the skin incision and lasted 48 h. We use morphine as rescue drug, which is given according to the patient’s pain situation. At the same time, the drug dosage of the patient’s analgesia pump used and morphine dosage are recorded. Three months after operation, the same doctor will call the patient again for follow-up. All data collected during this clinical study will be entered and/or filed in the patients’ CRFs. The patients’ study participation must be documented appropriately in the CRF with their study number, subject number, date of subject information, informed consent, and date of each visit. Source data will be filed according to the GCP guidelines. The data manager will be responsible for data processing, following the sponsor’s standard operating procedures.

Regular monitoring will be conducted to ensure that the data are adequate, accurate, and complete. The database will be locked only after the completion of quality assurance procedures.

### Statistical methods

#### Data selection for statistical analysis

Full analysis set (FAS): According to the principle of intention-to-treat analysis, a full analysis set will include all subjects who will enroll in the study and receive at least one treatment dose.Per-protocol set (PPS): The PPS population will include all FAS patients without major protocol deviations that influence the evaluation of the primary outcome. The efficacy analysis will be performed on FAS and PPS.Safety analysis set (SAS): The safety population consists of all subjects who will receive at least one treatment dose. Safety data analysis will be based on the safety population.

### Statistical analysis

All statistical tests are conducted by two-sided test, and the difference tested will be considered to be statistically significant if *P* ≤ 0.05(unless otherwise specified). The primary outcome measure will be statistically analyzed by chi-square or Fisher exact probability. Secondary outcome measures will be tested by group t-test. The description of quantitative indicators will calculate the mean, standard deviation, median, minimum, and maximum. The number and percentage of patients are used to statistically describe the demographic information, medical history, combined diseases and symptoms, physical examination, operation time, etc. According to the numerical characteristics of variables, *t*-test/Wilcoxon rank sum test is used to compare the quantitative data of age, height, and weight between the two groups; chi-square test/exact probability method is used to compare the categorical variables such as gender, medical history, combined diseases and symptoms, physical examination and so on.

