### Objectives

The purpose of this study is to determine whether the perioperative intervention with probiotics on intestinal flora can reduce the occurrence of POCD and to provide new ideas for its clinical prevention and treatment. Our primary objective is to assess the incidence of POCD 7 days after surgery. Our secondary objective is to assess the incidence of POCD and postoperative delirium (POD) 1 month and 7 days after surgery, respectively. We predict that probiotic intervention will reduce its incidence in elderly patients undergoing orthopedic surgery.

The schedule of the major study events for each visit is shown in Fig. 1. Patients who are scheduled to undergo orthopedic surgery will be included in this study. The entire process of recruitment and consenting of study participants by members of the research team will be consistent with good clinical practice (GCP) recommendations. Patients will be recruited mainly from the three centers.

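### The t-test prescribed for all secondary outcomes does not fit delirium incidence, which is yes/no; the result could change only if delirium events are sparse

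*Protocol article*

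**What the plan says.** All references are to the Protocol article.

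- **Test for secondary outcomes** (Statistical analysis): "Secondary outcome measures will be tested by group t-test". No secondary outcome is excepted.
- **Tests for other binary or categorical data** (same paragraph): "The primary outcome measure will be statistically analyzed by chi-square or Fisher exact probability", and for baseline characteristics "chi-square test/exact probability method is used to compare the categorical variables". No rule is given for choosing between chi-square and the exact test. Tests are two-sided, and P at or below 0.05 counts as significant.
- **First secondary outcome** (Secondary outcome measures): "Secondary outcomes comprise the following:Incidence of POD". Participant timeline makes this a yes/no classification: "The diagnosis of delirium by CAM requires the presence of features 1 and 2 and either 3 or 4".
- **Second secondary outcome** (same list): 1-month cognitive status, which "will be evaluated via TICS-m in 1 month after surgery". Participant timeline adds "The TICS-m score ranges from 0 to 48" and gives no cut-off for cognitive dysfunction.
- **Objectives** words the 1-month aim differently: "Our secondary objective is to assess the incidence of POCD and postoperative delirium (POD) 1 month and 7 days after surgery, respectively". The Abstract also words it as an incidence.

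**The concern.** A test of means is assigned to a set of outcomes that includes a proportion. This is a stated rule that does not fit the variable, not a detail left for later. It also treats like data in two ways: POCD at day 7, a yes/no outcome, gets chi-square or Fisher, while delirium at day 7, also yes/no, gets a t-test.

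What is at stake is the delirium verdict. When events are few, a t-test on 0/1 data and Fisher's exact test can fall on opposite sides of 0.05. Sparse events are conceivable here: delirium assessment is scheduled at day 7 only, in elective patients of ASA grade I–II with MMSE below 24 excluded. The protocol gives no delirium rate, however, so this is an assumption. If the sentence is left as it stands, the analyst must either follow an ill-fitting rule or choose a test once the counts are known.

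**Working it through.** **Inputs.** Allocation is 1:1 (Randomization). There are 100 evaluable and 110 enrolled per group (Sample size). The threshold is two-sided 0.05 (Statistical analysis). Delirium rates are not given; 2% to 10% is assumed.

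**1. The plan's own figure.** The protocol sizes only the primary outcome, at 25% vs 10% with power 0.80. With pooled variance under the null and mean rate 0.175:

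n = [1.960·√(2·0.175·0.825) + 0.842·√(0.25·0.75 + 0.10·0.90)]² / 0.15² = (1.053 + 0.443)² / 0.0225 ≈ 99.5, rounded up to 100.

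The stated 100 per group is reproduced. No figure is stated for the secondary outcomes.

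**2. One split by hand: 0 vs 4 events, 110 per arm.**

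- *Pooled t-test on 0/1 data.* p₁ = 0 and p₂ = 4/110 = 0.03636. s² = n[p₁(1−p₁) + p₂(1−p₂)]/(2n−2) = 110·0.03504/218 = 0.01768. T = 0.03636/√(0.01768·2/110) = 2.028 on 218 df, P = 0.0438.
- *Uncorrected chi-square.* Pooled rate 4/220 = 0.01818. z = 0.03636/√(0.01818·0.98182·2/110) = 2.018, P = 0.0435.
- *Fisher, two-sided.* 2·(110·109·108·107)/(220·219·218·217) = 0.122.
- *Smallest expected count.* 4/2 = 2, so a below-5 rule would select Fisher.

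**3. All splits where the t-test and Fisher disagree when an expected count is below 5** (110 per arm; the same three splits flip at 100):

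| Events | Smallest expected | t-test | Chi-square, uncorrected | Fisher |
|---|---|---|---|---|
| 0 vs 4 | 2.0 | 0.0438 | 0.0435 | 0.122 |
| 0 vs 5 | 2.5 | 0.0237 | 0.0237 | 0.060 |
| 1 vs 7 | 4.0 | 0.0308 | 0.0307 | 0.065 |

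In each, the t-test is significant and Fisher is not. At 0 vs 6 and 1 vs 8 they already agree. If Fisher were used at every count, further splits would flip, for example 2 vs 9 (0.030 vs 0.059) and 4 vs 12 (0.038 vs 0.066). Against uncorrected chi-square, the only disagreement found at 110 per arm is the borderline 33 vs 47 (0.0500 vs 0.0497).

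**4. How often the verdict differs.** Binomial probabilities were summed over the event splits at 100 per arm. The comparator is chi-square, or Fisher when an expected count is below 5.

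| Assumed rates | t-test rejects | Chi-square/Fisher rejects | Verdicts differ |
|---|---|---|---|
| 2% vs 2% | 4.0% | 0.5% | 3.5% |
| 3% vs 3% | 4.5% | 1.3% | 3.2% |
| 5% vs 5% | 4.4% | 3.3% | 1.1% |
| 10% vs 10% | 5.2% | 5.2% | about 0% |
| 5% vs 1% | 37.2% | 20.1% | 17.0% |
| 6% vs 1% | 49.1% | 33.0% | 16.2% |
| 8% vs 2% | 49.0% | 43.2% | 5.8% |
| 10% vs 4% | 38.7% | 38.0% | 0.7% |
| 10% vs 5% | 27.0% | 26.7% | 0.3% |

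The first four rows are type I error rates. The t-test's lie between 4.0% and 5.2%, the same as those of uncorrected chi-square.

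**The case against.** The strongest reply is that the choice hardly matters. The protocol's binary rule is chi-square or Fisher with no switching rule, and uncorrected chi-square gives practically the same P value as the t-test in every split shown. The gap at low counts largely reflects Fisher's conservatism (0.5% rejection at a common rate of 2%), not excess false positives from the t-test. This stands, and it limits the point to fit, consistency and advance specification. It does not remove it: expected counts in the flipped splits are 2 to 4, where Fisher is the conventional choice, and the protocol names Fisher for its other binary outcome.

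Three stronger readings are tempting and are not supported.

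- *That the t-test's normal approximation breaks down and produces false positives.* The error rates above show no material inflation.
- *That a t-test leaves delirium without an effect estimate.* On 0/1 data it estimates the risk difference with a Wald-type interval. The interval is poor at sparse counts, but it exists. The sentence on the primary outcome names no effect measure either, and an analysis plan that is not shown may supply one.
- *That 1-month POCD is certainly mis-tested too.* Objectives and the Abstract call it an incidence, but the outcome list gives only TICS-m status and no cut-off is stated. If the score is what is analysed, a t-test is reasonable. The defect there is an inconsistent definition.

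It can also be said that this is one overbroad sentence in a condensed article. That bears on severity; the sentence still states a rule, and the rule is wrong for one of the two outcomes listed.

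**Conclusion.** The point holds for delirium and should be fixed, but it is not critical. The stated test does not fit a yes/no outcome and contradicts the practice of its own paragraph. The consequence is confined to sparse events: three splits of at most eight events in total under the expected-count rule, and only relative to Fisher. How likely that is depends on a delirium rate the documents do not give. Disagreement runs from about 17% of trials at 5% vs 1% to under 1% at 10% vs 5%, assuming 100 evaluable per arm and Fisher when an expected count is below 5. For 1-month POCD the point is conditional on that outcome being kept as an incidence. The primary outcome, its test and the sample size are not touched.

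**What to change.** Replace the sentence on secondary outcomes in Statistical analysis with:

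> Incidence of POD will be compared by chi-square test, or Fisher's exact test when any expected count is below 5, with risk difference and 95% CI; the 1-month TICS-m score will be compared by t-test.

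Then reconcile the Abstract and Objectives (incidence of POCD at 1 month) with Participant timeline and Secondary outcome measures (TICS-m cognitive status, no cut-off). If 1-month POCD is kept as an incidence, define the criterion for a case and analyse it by the same chi-square/Fisher rule.

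The cost is one sentence plus one definition to settle. No extra data or patients are needed. The change should be made before unblinding, so that the test is not chosen with the counts in view.
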